### 6.1.3 End of Treatment Procedures and Long-Term Follow-Up

Patients who discontinue therapy for any reason must have an end of treatment (EOT) visit completed 28 days ( $\pm$  7 days) after the last application of study drug. Following the end of treatment, subjects will be followed for survival and progression for 2 years.

At the EOT visit, the patients will undergo the following assessments:

|                                              |                                                                                                                                                                                                                                |
|----------------------------------------------|--------------------------------------------------------------------------------------------------------------------------------------------------------------------------------------------------------------------------------|
| Pregnancy Test (if applicable)        | FCBP pregnancy testing required at treatment discontinuation and at 28 days following treatment discontinuation. If menstrual cycles are irregular, additional testing 14-days following treatment discontinuation is required |
| Physical Examination and Vital Signs  | 
 
• Body weight
 
• Blood pressure, pulse, temperature
 
• Physical examination
 
• Pulse oximetry to investigator discretion
 
                             |
| Hematology                            | Hemoglobin, hematocrit, WBC count, WBC differential, red blood cell count, platelets. WBC differential may be automated or manual as per institutional standards.                                                              |
| Clinical Chemistry                    | Sodium, potassium, chloride, bicarbonate, BUN, creatinine, glucose, uric acid, total protein, albumin, calcium, phosphorus, magnesium, total bilirubin, alkaline phosphatase, ALT, AST, LDH.                                   |
| Myeloma Disease Assessment–Laboratory | M-protein determination: 
 
• Serum protein electrophoresis and immunofixation
 
                                                                                                  |

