#### **6.4 Instructions for Initiation of a New Cycle**

A new course of treatment may begin on the scheduled Day 1 of a new cycle if all of the following are met:

- $ANC \geq 1.0 \times 10^9/L$
- Platelet count  $\geq 30 \times 10^9/L$
- Any other study drug-related adverse event must have resolved to Grade 1 or baseline (see Appendix 2)
- Serum uric acid and creatinine concentrations must return to baseline prior to carfilzomib doses during Cycles 1 and 2

If  $ANC < 1.0 \times 10^9/L$  but  $> 0.75 \times 10^9/L$ , the start of a new cycle is at the discretion of the treating investigator

If these conditions are not met on Day 1 of a new cycle, the subject will be evaluated weekly, and a new treatment cycle will not be initiated until the toxicity has resolved, as described above.

If daratumumab, carfilzomib, or lenalidomide, or daratumumab are held for the remainder of the previous cycle or the new cycle is delayed due to residual toxicity on the planned Day 1 of the next cycle, then the new cycle will be started at 1 dose decrement.

If a delay of starting a new cycle is greater than 21 days, the subject should be discontinued from treatment, unless continuing treatment is mutually agreed upon by the site Lead Principal Investigator at the University of Chicago and the co-investigator at the treating institution.

Dexamethasone may be discontinued without the subject discontinuing study treatment.

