## 6.5 Dose-modification guidelines

The following sections and tables summarize dosing modifications of daratumumab, carfilzomib, lenalidomide and dexamethasone to manage possible toxicity. Dose modifications different from those stated in the protocol should be discussed with the Lead Principal Investigator. Administration of daratumumab, carfilzomib and lenalidomide will be discontinued in the event of any other toxicity that, in the opinion of the lead, secondary site, or treating investigator, warrants discontinuation.

In addition to dose reductions, administration of daratumumab, carfilzomib and lenalidomide will be held temporarily in the event of a treatment-related toxicity at the treating investigator's discretion.

Study treatment may be reintroduced if resolution of the event to the baseline value or to  $\leq$  Grade 1 within 21 days; otherwise study drug will be permanently discontinued. Any deviations from this plan must be approved by the Lead Principal Investigator.

All clinically-significant non-hematologic toxicities must be resolved to Grade 1 or baseline.

Individual dose modification of daratumumab is not permitted. Dosing can be delayed to manage daratumumab-related toxicities. Dose de-escalation of daratumumab will be based only on the Data and Safety Monitoring Board (DSMB) recommendation. Dose reduction levels of carfilzomib, lenalidomide and dexamethasone for toxicity management of individual subjects are provided below:

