| Infection Grade 3 or 4                                                                                                                                                                                                                                                                 | 
Hold lenalidomide until systemic treatment for infection is completed. If no neutropenia, restart both drugs at full dose. If neutropenic, follow neutropenic instructions.
                    | 
Hold carfilzomib until systemic treatment for infection is completed. If no neutropenia, restart both drugs at full dose. If neutropenic, follow neutropenic instructions.
 |
| Herpes zoster or simplex of any grade                                                                                                                                                                                                                                                  | 
Hold lenalidomide until lesions are dry.
 
Reinstitute at full doses.
                                                                                                                     | 
Hold carfilzomib until lesions are dry.
 
Reinstitute at full doses.
                                                                                                  |
| Grade 2 neuropathy with pain or any Grade 3 neuropathy                                                                                                                                                                                                                                 | 
Hold until <math>\leq</math> Grade 2.
 
Then restart lenalidomide at 1 dose decrement
                                                                                                     | 
Hold until resolved to <math>\leq</math> Grade 2.
 
Then restart carfilzomib at 1 dose decrement
                                                                      |

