| Hyperthyroidism or hypothyroidism                                                                                                                                                                                                                         | Omit lenalidomide for remainder of cycle, evaluate, and initiate appropriate therapy.

Restart lenalidomide next cycle at 1 dose decrement                                                                                                                                                                                  | No adjustment required                                                                                                                                                                                                                                                                                                          |
| Congestive heart failure (CHF)                                                                                                                                                                                                                                   | Any subject with symptoms of CHF, whether or not lenalidomide related, must have the dose held until resolution or return to baseline. If CHF was felt to be lenalidomide related, reinstate by one dose decrement after return to baseline. If no resolution of CHF after 2 weeks, the subject will be withdrawn from the study. | Any subject with symptoms of CHF, whether or not carfilzomib related, must have the dose held until resolution or return to baseline. If CHF was felt to be carfilzomib related, reinstate by one dose decrement after return to baseline. If no resolution of CHF after 2 weeks, the subject will be withdrawn from the study. |

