## 6.6 Treatment Discontinuation

Subjects will be free to discontinue treatment or withdraw from the study at any time, for any reason, or they may be withdrawn/ removed if necessary in order to protect their health (see reasons for withdrawal below).

Patients will be removed from further treatment for the following reasons:

- Disease Progression
- Non-compliance with study procedures
- Subject no longer consents to participate in the study
- Intercurrent illness that interferes with study assessments
- Treatment-related toxicity requiring treatment discontinuation
- Incidence or severity of AEs that indicates a potential health hazard to the subject
- For the fourth occurrence of the same Grade  $\geq 3$  non-hematological toxicity
- A delay in treatment > 21 days unless approved by the Lead Principal Investigator, or due to congestive heart failure unresolved for > 28 days the treatment shall be discontinued ([see Table 6-8](#))
- Treating investigator discretion
- Requirement for alternative therapy
- Suspected or positive pregnancy
- Termination of the study by the sponsor

The Lead Principal Investigator should be contacted regarding any impending discontinuation of a study subject. If the reason for withdrawal is the occurrence of an AE, the subject will be followed until such events resolve, stabilize, and, according to the treating investigator's judgment, there is no need for further follow up. The reason for withdrawal from study must be documented in the case report form.

Any Grade 5 toxicity related to study treatment will prompt stopping of the trial until further review is completed. Additionally, development of Grade 4 of non-hematologic toxicities in 2 or more patients will prompt the DSMB to stop the study for review to determine whether the trial should be terminated due to excessive toxicity.

In case of premature discontinuation of the study treatment, the investigations scheduled for the EOT should be performed, if possible. Should a patient decide to withdraw, every effort will be made to complete and report the observations as thoroughly as possible. The treating investigator should contact the patient to determine as completely as possible the reason for the withdrawal. A complete final evaluation at the time of the patient's withdrawal should be made, with an explanation of why the patient is withdrawing from the study.

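### Table 6-8 and Section 6.6 set different stopping limits for congestive heart failure (2 weeks against more than 28 days), and the Table 6-8 hold for painful Grade 2 neuropathy is released at Grade 2

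*Protocol*

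**What the plan says.** **CHF.** The CHF row of Protocol Table 6-8 requires the dose to be held for any subject with symptoms, related to the drug or not, until the event resolves or returns to baseline. If CHF is attributed to the drug, dosing resumes one level lower. Both drug columns then end: "If no resolution of CHF after 2 weeks, the subject will be withdrawn from the study".

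Section 6.6 lists reasons for removal from treatment. One item combines a general delay limit, "A delay in treatment > 21 days unless approved by the Lead Principal Investigator", with a CHF limit, "due to congestive heart failure unresolved for > 28 days the treatment shall be discontinued", and refers the reader to Table 6-8.

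**General 21-day rules.** Section 6.5 allows study treatment to be reintroduced after a treatment-related toxicity if it recovers to baseline or to "Grade 1 within 21 days; otherwise study drug will be permanently discontinued". Section 6.4 says: "If a delay of starting a new cycle is greater than 21 days, the subject should be discontinued from treatment", unless the lead and treating investigators agree to continue.

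**Neuropathy.** The Table 6-8 trigger is "Grade 2 neuropathy with pain or any Grade 3 neuropathy". Both drugs are held until the event is Grade 2 or lower. For lenalidomide the instruction continues: "Then restart lenalidomide at 1 dose decrement"; the carfilzomib cell has the same reduction. Sections 6.4 and 6.5 require non-hematologic toxicity to have recovered to Grade 1 or baseline (in 6.4, any other drug-related event; in 6.5, any that is clinically significant).

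**The concern.** Section 6.6 sends the reader to Table 6-8 for the CHF rule, and the table gives half the time. The usual principle that a specific rule overrides a general one does not help, because both clauses name CHF. Two sites acting in good faith could treat the same recovered patient differently: one ends treatment at 2 weeks, the other waits and restarts.

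The event matters for this regimen. Section 1.3.1 lists cardiovascular effects among the dose-limiting toxicities of carfilzomib in animals, and Section 1.4 lists CHF among reported lenalidomide events. Exclusion 15 bars NYHA Class III or IV heart failure, so milder disease is not excluded by that criterion.

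For neuropathy, a hold whose release condition is already satisfied when it begins asks for no improvement before restart.

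At stake are patient safety at restart and a consistent record of why treatment stopped. Sample size, power and the primary test are not involved.

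**Working it through.** There is no stated figure to reproduce. The check sets the rules side by side.

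**1. The two CHF limits.** The protocol does not say when the clock starts; I assume onset of CHF.

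| Source | Limit | Consequence |
|---|---|---|
| Table 6-8, CHF row, both columns | unresolved after 2 weeks (14 days) | leaves the study |
| Section 6.6, CHF clause | unresolved for more than 28 days | treatment stops |

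- Resolution by day 14: neither limit is reached. No conflict.
- Resolution on days 15 to 28: the Table 6-8 limit is passed and the Section 6.6 CHF limit is not. Width: 28 − 14 = 14 days.
- Still unresolved after day 28: both limits are passed.

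In all three cases Table 6-8 holds the dose until resolution or return to baseline. The conflict is therefore about restart after recovery.

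**2. Is 21 days a third CHF limit?** The general rules count different things:

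- Section 6.4 counts delay in starting a new cycle.
- Section 6.5 counts time to recovery, for treatment-related toxicity only. The CHF row applies whatever the cause.
- Section 6.6 counts delay in treatment.

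Example: CHF begins on Day 8 of a 28-day cycle and lasts 28 days. It ends on day 8 + 28 = 36, counted from Day 1 of that cycle. The next cycle was due on day 29, so the new-cycle delay is 36 − 29 = 7 days, well under 21. The same episode that runs right up to the 28-day CHF limit does not reach the Section 6.4 limit. The 21-day rules do not line up on one axis with the 14- and 28-day limits.

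**3. Neuropathy.** Grades of improvement needed before restart = grade at hold − highest grade allowed at release.

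| Grade at hold | Table 6-8 (release at Grade 2 or lower) | Sections 6.4 and 6.5 (release at Grade 1) |
|---|---|---|
| Grade 2 with pain | 2 − 2 = 0 | 2 − 1 = 1 |
| Grade 3 | 3 − 2 = 1 | 3 − 1 = 2 |

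The *or baseline* alternative does not close the gap, because exclusion 10 bars peripheral neuropathy of Grade 2 or higher at screening.

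The hypertension and pulmonary hypertension rows of the same table also release carfilzomib at Grade 2 or lower, but they hold at Grade 3 or higher and so require at least 3 − 2 = 1 grade of improvement. Only the painful Grade 2 trigger requires none.

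**The case against.** The strongest reply is that the rules can all be obeyed at once. Section 6.6 lists reasons for removal; it grants no permission to continue, and it does not say that CHF leads to a stop only after 28 days. For treatment-related CHF, the 2-week rule in Table 6-8 arguably triggers another item in the same list, on toxicity that requires discontinuation. A site that always applies 2 weeks breaks nothing. This stands as far as it goes. It does not remove the mismatch: Section 6.6 cites the table for a limit that the table does not contain, and no text says that the stricter figure governs.

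A reader might infer three competing CHF limits of 14, 21 and 28 days, with a distinct outcome in each 7-day band. The protocol does not support that. The 21-day rules run on different clocks, and Section 6.5 covers only treatment-related events and is permissive about reintroduction.

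A reader might also infer that patients could be re-dosed during active heart failure. The hold until resolution rules that out. In addition, drug-related CHF restarts one level lower, the Lead Principal Investigator should be contacted about any impending discontinuation (Section 6.6), and deviations from the Section 6.5 plan need that investigator's approval.

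On neuropathy, the objection is that Sections 6.4 and 6.5 already require recovery to Grade 1 or baseline and so supply what the row omits. That is a sensible reading, but it means that the row contradicts the general rule. The author may have meant Grade 2 without pain; the row does not say so.

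On the CHF consequence, the difference between leaving the study and stopping treatment is largely one of wording. Section 6.1.3 says: "Patients who discontinue therapy for any reason must have an end of treatment (EOT) visit", and Section 6 provides survival follow-up for subjects taken off treatment for other reasons.

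**Conclusion.** The point holds in two parts. First, two CHF-specific limits, 14 days and more than 28 days, conflict, and restart is unsettled for CHF that resolves on days 15 to 28 (14 days, counted from onset by assumption). Second, the neuropathy row requires no improvement before restart from painful Grade 2, against one grade under Sections 6.4 and 6.5; the one-level reduction is unaffected.

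The general 21-day rules are a secondary matter to reconcile when the CHF text is edited.

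The practical size is small. The number of patients affected is unknown and may be zero. Section 6.3.5 says that all patients will be switching from the intravenous formulation, with no new starts, which suggests that exposure under this version is limited to patients already on treatment. The primary sCR/MRD analysis is unaffected. The correction is still worth making because these are safety rules in force.

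**What to change.** 1. State one CHF limit in both Table 6-8 (both columns) and Section 6.6. The default should be the stricter 2 weeks. If a longer limit is wanted, say how it relates to the 21-day rules in Sections 6.4, 6.5 and 6.6, and say when the clock starts.
2. Give the consequence in Table 6-8 as *discontinued from study treatment*, so that the end-of-treatment visit and follow-up plainly apply.
3. In the neuropathy row, change the release for both drugs to *Grade 1 or baseline*. If the intent was *Grade 2 without pain*, write that and mark it as an exception in Sections 6.4 and 6.5. Keep the one-level dose reduction.

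The cost is amendment wording in Table 6-8 and Section 6.6, plus a line each in Sections 6.4 and 6.5 if an exception is chosen. No extra visits, procedures or patients are needed.

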**Table 6-8 Dose Modifications for Non-hematologic Toxicity**

| Recommended Action                                                                                                                                                          |                     |                                                                                                                                                                                                                                                                          |
|------------------------------------------------------------------------------------------------------------------------------------------------------------------------------------|---------------------|--------------------------------------------------------------------------------------------------------------------------------------------------------------------------------------------------------------------------------------------------------------------------|
|                                                                                                                                                                                    | Lenalidomide | Carfilzomib                                                                                                                                                                                                                                                       |
| Pericardial Effusion                                                                                                                                                        | NA                  | ≥ Grade 3: carfilzomib attribution, hold drug until resolved to Grade 1. Resume at one level dose reduction                                                                                                                                                              |
| Pericarditis                                                                                                                                                                | NA                  | ≥ Grade 3: carfilzomib attribution, hold drug until resolved to Grade 1. Resume at one level dose reduction                                                                                                                                                              |
| Thrombotic Microangiopathy (TMA)                                                                                                                                            | NA                  | Monitor for signs and symptoms of TTP/HUS. If the diagnosis is suspected, stop carfilzomib and evaluate. If the diagnosis of TTP/HUS is excluded, carfilzomib may be restarted. If carfilzomib related TMA is confirmed, carfilzomib should be discontinued permanently. |
| Posterior Reversible Encephalopathy Syndrome (PRES)                                                                                                                         | NA                  | Discontinue carfilzomib if PRES is suspected and evaluate.                                                                                                                                                                                                               |
| Pulmonary Hypertension                                                                                                                                                      | NA                  | = Grade 2: carfilzomib attribution, Reduce drug: one level dose reduction

≥ Grade 3: carfilzomib attribution, hold drug until resolved to ≤Grade 2. Resume at one level dose reduction                                                                            |
| Pulmonary Toxicities: Interstitial Lung Disease (inc. pneumonitis), Acute Respiratory Failure, and Adult Respiratory Distress Syndrome (ARDS), cough, and cough with phlegm | NA                  | ≥ Grade 2 for Pneumonitis

≥ Grade 3 for ARDS

≥ Grade 4 for Respiratory Failure

carfilzomib attribution, hold drug until resolved to ≤Grade 1. Resume at one level dose reduction                                                                    |

